**Methods:**

More than 18,000 customers of a large Swiss health insurance company were allocated to a financial incentive, a charitable incentive, or a control group and invited to participate in a health prevention program. Participants used a pedometer to track their daily physical activity over the course of 6 months. A Web-based questionnaire was administered at the beginning and at the end of the intervention and additional data was provided by the insurance company. The primary outcome of the study will be the participation rate, secondary outcomes will be adherence to the prevention program, physical activity, and health status of the participants among others.

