**Results:**

Baseline characteristics indicate that residence of participants, baseline physical activity, and subjective health should be used as covariates in the statistical analysis of the secondary outcomes of the study.

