### Data Collection and Variables

Data for analysis is partly collected by submission of information by the participants via the Web-based platform of the insurance company and partly by administering a Web-based questionnaire at 2 different points in time (T_1_ and T_2_) over the course of the intervention. After participants registered their pedometer or smartphone at the Web-based platform of the insurance company, the number of steps were synchronized automatically with the Web-based platform each day at midnight. However, participants could choose to deactivate automatic synchronization and enter their step count manually on the Web-based platform. Days where no step data is available (eg, because the pedometer was not worn or not charged) will be treated as missing data. The first measurement (T_1_) is set at the beginning of the PHI for all groups, whereas the second measurement (T_2_) is set at the end of the intervention for the experimental groups and after the first half of the intervention for the control group before they received financial incentives. Additional data, such as age, gender, or participants’ health service billings, were provided by the insurance company. To guarantee appropriate response rates, participants received additional $5 for each time they completed the questionnaire resulting in an additional bonus of $10. See Figure 1 for an overview of the study design.

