### Data Analysis

Due to the nested structure of the data, mixed-effect models will be used for data analysis. As measurements are nested within participants, the step count measurements represent the level 1 unit of analysis, whereas the participants represent the level 2 unit of analysis. A recent article [73] discusses the problem of faking with regard to financial incentives, (eg, faking step counts in order to qualify for financial rewards). This problem applies to our study as step counts could be entered manually. Step count measurements that are unusually high and were manually entered are likely to represent a tendency of faking. Thus, univariate and multivariate outlier analysis [74] will be conducted in order to identify participants that are prone to faking. Changes on outcomes solely measured at T_1_ and T_2_ will be analyzed performing a repeated-measures analysis of variance (rmANOVA). The analyses will be conducted using the nlme-package [75] in R [76] and the typical significance level of α = 5% will be applied.

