### Baseline Characteristics

Table 1 presents the baseline characteristics of all T_1_ survey participants for each of the different EGs. Unfortunately, participants’ service billings with the health insurance company were not yet available at the time of writing. Between-group comparisons are based on one-way ANOVA for continuous variables and on chi-square tests for categorical variables. Due to the large number of participants, even small between-group differences are likely to become statistically significant. Hence, effect sizes are reported for between-group comparisons.

Participants were mostly Swiss (1195/1319, 90.60%), living in a village or on the countryside (836/1319, 63.38%), holding a university degree (597/1319, 45.26%), and were 43-years old on average (M=42.95, SD = 13.11). Slightly more men than women participated in the T_1_ survey (638/1319, 48.14% vs 585/1319, 44.35%). A Fitbit pedometer or the Fitbit app was most often used for tracking physical activity (1116/1319, 84.61%) and more than half of the participants (709/1319, 53.75%) bought a pedometer in order to participate in the PHI.

While baseline characteristics show no meaningful group differences regarding age, gender, education, income, nationality, self-reported physical activity at work and during spare time, walking on the way to work, pedometer brand, prior possession of a pedometer, and participation of a family member or friend, group differences could be observed regarding residence of participants, self-reported physical activity and walking, and subjective health status. Differences regarding residence of participants indicate that matching groups according to population density may not be sufficient to account for residence differences.

Because these baseline characteristics are related to physical activity they are primarily relevant for the analysis of the secondary outcomes of the study. Consequently, residence of participants and subjective health status will be used as covariates in the statistical analyses of the secondary outcomes. Because mixed-effects models will be used for data analysis, group differences regarding baseline physical activity will be directly modelled by allowing different intercepts for the experimental groups.

**Table 1 table1:** Demographics and baseline characteristics.

Charachteristic^a^			Total (*N*=1319)	Financial incentives/ EG1 (*n*=626)	Charitable incentives/ EG2 (*n*=562)	Control group/ CG (*n*=131)	*P*	Effect size^b^

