## Discussion

### Strengths and Limitations

This study protocol describes the design and baseline characteristics of a longitudinal cluster-randomized controlled trial testing the effects of monetary and charitable incentives on the acceptance of and adherence to a pedometer-based health prevention program. To the best of our knowledge, this is the first study to systematically test the effects of different incentive strategies within a pedometer-based health intervention offered by a large health insurance company in western cultures. External validity has to be pointed out as a key strength of the described trial. Both study design and incentive strategies are tested in a real-world setting, thus ensuring the applicability of the results and conclusions.

When interpreting the results of this study, some limitations have to be considered: selection effects might affect the participation in the PHI. For example, by especially attracting highly motivated or physically active participants, those effects could potentially undermine the power of our analyses. However, we will be able to control our analyses for prior level of physical activity. Further, comparisons of T_2_ measures between the groups have to be interpreted with caution, because T_2_ reflects different time points for experimental and control groups. T_2_ was set at 6 months after start of the intervention for the EGs and at 3 months for the CG. However, the main focus of this study is on the acceptance of the promotion program, which is operationalized using the participation rate, and is thus not dependent on any T_2_ measurement. Lastly, the goal of reaching 10,000 steps per day on average might have detrimental motivational effects for some participants. It might be perceived as too challenging for very inactive participants or when participants were not able to achieve sufficiently high step counts for several days in a month.

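### Arm-specific intercepts in the step-count model cannot serve as baseline adjustment, because in months 1-3 they mix prior activity differences with any immediate incentive effect

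*Protocol article*

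**What the plan says.** Methods, Data Analysis, sets up a mixed-effects model in which "the step count measurements represent the level 1 unit of analysis, whereas the participants represent the level 2 unit of analysis". The abstract gives the tracking period: "Participants used a pedometer to track their daily physical activity over the course of 6 months". On data capture, Data Collection and Variables states: "After participants registered their pedometer or smartphone at the Web-based platform of the insurance company, the number of steps were synchronized automatically".

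Experimental Groups entitles both incentive arms (EG1 and EG2) to monthly rewards and describes no unrewarded opening period for them. The control group (CG) has no reward in months 1-3. In months 4-6 it can earn $20 or $10 per month, against $10 or $5 in the incentive arms, and it is not told of this in advance.

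The article makes three statements on prior activity:

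- Abstract, Results: "residence of participants, baseline physical activity, and subjective health should be used as covariates".
- Results, Baseline Characteristics: "residence of participants and subjective health status will be used as covariates in the statistical analyses of the secondary outcomes". Activity is left out of that list and is handled instead by the arm intercepts: "group differences regarding baseline physical activity will be directly modelled by allowing different intercepts for the experimental groups".
- Discussion, Strengths and Limitations, in reply to the worry that active people will self-select: "we will be able to control our analyses for prior level of physical activity".

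**The concern.** An arm-specific intercept can stand for a baseline difference only if the outcome series starts before the arms are treated differently. Here the step series starts with the programme, when EG1 and EG2 already work under their incentive and CG does not. The intercept difference is then an early on-treatment difference.

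Two things are at stake for the step outcome. If the analyst takes the arm intercept as a nuisance baseline term, an incentive that raises steps at once and keeps them raised is set aside as a pre-existing difference. If the analyst takes it as the effect, nothing in the model adjusts for prior activity, although the article itself reports that the arms differ on it.

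The second problem is not cured by randomisation. Cantons were randomised, but steps exist only for people who joined, and joining is what the incentive is meant to change.

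**Working it through.** **1. What the intercept estimates.** Take months 1-3 and code month m = 0, 1, 2, with arm = 1 for an incentive arm and 0 for CG:

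steps = a + b·arm + c·m + d·arm·m + participant effect + error.

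Let B be the difference between joiners that would exist without incentives, and E the immediate effect of the incentive. At m = 0 the expected arm difference is b = B + E. Step data supply one quantity for two unknowns. If the effect is constant, d = 0, whatever the split between B and E.

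**2. Numerical check.** The model was fitted by REML with a participant random intercept, using the T1 respondent counts in Table 1: 626 for EG1 and 131 for CG. The following are assumptions and do not come from the article: between-person SD 2500 steps, residual SD 1200, mean 8500, common trend -150 per month, 40 replicates. B + E was held at 1000 steps/day.

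| B | E | Fitted b (SD over replicates) | Fitted d (SD over replicates) |
|---|---|---|---|
| 0 | 1000 | 1002 (249) | -20 (87) |
| 1000 | 0 | 1002 (249) | -20 (87) |
| 500 | 500 | 1002 (249) | -20 (87) |
| -500 | 1500 | 1002 (249) | -20 (87) |

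The rows agree because only the sum B + E enters the data. A world with no incentive effect and a world with a 1500-step effect cannot be told apart. The 1000-step gap is an illustration.

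**3. Is B likely to be zero?** The article does not report the number of active participants, so T1 respondents per customer contacted (Table 1) serve as a proxy for uptake:

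- EG1: 626/7487 = 8.4%
- EG2: 562/8216 = 6.8%
- CG: 131/2935 = 4.5%

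Uptake that differs this much gives no reason to expect equal prior activity among joiners. Table 1 shows median walking of 6.54, 6.00 and 4.50 hours/week. Eta-squared is .03 for walking and .03 for moderate to vigorous activity, both at P < .001. By the table's own conventions (.01 small, .09 medium) that is nearer small than medium. It is still one of the differences that the article singles out for handling.

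**4. Why the contrast with control has to stop at month 3.** Suppose the incentive arm has a constant effect E, CG responds by F once it is rewarded, and months carry equal weight. The six-month mean difference is then B + [3E + 3(E - F)]/6 = B + E - F/2. With F = E, half of the effect disappears. Over months 1-3 the difference is B + E, and adjustment for measured prior activity acts on B.

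**5. The three statements side by side.** The abstract calls for a participant-level covariate. Baseline Characteristics names two covariates and gives activity to an arm-level term. Strengths and Limitations relies on control for prior activity. An arm intercept takes one value for everyone in the arm and uses no measurement made before the incentive, so it delivers neither of the other two.

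**The case against.** The strongest reply is that the article never says how the incentive effect will be read. It does not say that the effect is the arm-by-time slope or that the arm term will be discarded, and an arm term is also how an arm main effect is estimated. A condensed article may leave contrasts to a fuller document. This stands. A reader might infer that the plan loses the whole of a sustained effect, or turns a fading effect into apparent harm. That follows only if the slope is the sole effect measure, and the article does not say so.

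A second reply concerns the control group. A reader might infer that all step data were collected under an incentive. That is not so: CG steps in months 1-3 are unrewarded. A time-varying incentive indicator, equal to 1 except for CG in months 1-3, is not a linear combination of arm and month terms, so it can be estimated alongside arm intercepts. The simulation above used months 1-3 only and does not speak to this. But the contrast rests on parallel trends and on a common effect of rewards that differ in size ($20 against $10). It measures CG's response to the switch at month 4, gives EG1 and EG2 no pre-incentive baseline, and is not described in the article.

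Third, all three statements show the same intent to adjust. That is true and makes the contradiction easy to settle, but the mechanism that is actually fixed does not carry out the intent.

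Finally, Figure 1 is not available, so a run-in shown only there cannot be excluded. The text describes none.

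**Conclusion.** The concern holds for the step-count mixed model. In months 1-3 the rewarded-minus-control intercept is the prior difference plus any immediate incentive effect, and step data alone cannot separate the two. Calling it baseline adjustment is wrong under either reading, and it conflicts with the abstract and with Strengths and Limitations.

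The size of the resulting error cannot be derived from the article, which gives no step data. The bias is E if the intercept is read as baseline, and B if it is read as the effect.

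Severity is moderate. Step count is a named indicator of a secondary outcome. The participation rate is untouched, and outcomes analysed by repeated-measures ANOVA have a measured T1 value. The conclusion assumes that step capture began with the programme, as the text indicates.

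**What to change.** - Reconcile the abstract, Baseline Characteristics and Strengths and Limitations so that one method of handling prior activity is stated.
- In the step model, enter T1 self-reported moderate to vigorous activity and walking hours as participant-level covariates, log-transformed as already done for Table 1, alongside residence and subjective health.
- Keep arm terms in the model, but stop describing them as baseline adjustment.
- Define the EG-versus-CG incentive effect as the covariate-adjusted arm contrast in mean or month-specific steps over months 1-3, before CG is rewarded.
- State how missing T1 responses are handled, for example by multiple imputation. A missing-value indicator is weaker here, because joiners are not balanced by randomisation.

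The cost is wording plus the missing-data rule, since the T1 variables are already collected. The adjustment will be partial: T1 activity is self-reported, skewed, and recorded at programme start after arm-specific invitations, and self-selection on unmeasured traits remains. The article should say so when it interprets step differences.

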**Group characteristics**								
	Number of cantons		26	8	11	7		
	Number of customers contacted		18,638	7487	8216	2935		
	Population density^c^ (residents/km^2^, median)		233.56	255.15	173.45	221.08		
**Demographic variables**								
	Age		42.95 (13.11)	43.06 (13.25)	42.50 (12.88)	44.37 (13.40)	.36	.002
	Gender (%)						.89	.01
		Female	585 (44.35)	285 (45.53)	244 (43.42)	56 (42.75)		
		Male	635 (48.14)	301 (48.08)	270 (48.04)	64 (48.85)		
		Not declared	99 (7.51)	40 (6.39)	48 (8.54)	11 (8.40)		
	Education^d^ (%)						.17	.10
		University	597 (45.26)	301 (48.08)	244 (43.42)	51 (39.69)		
		Professional School	421 (31.92)	194 (30.99)	188 (33.45)	39 (29.77)		
		High School	219 (16.60)	95 (15.18)	95 (16.90)	29 (22.14)		
		Secondary School	25 (1.90)	13 (2.08)	10 (1.78)	2 (1.53)		
		Primary School	6 (0.45)	4 (0.64)	1 (0.18)	1 (0.76)		
		Not declared	51 (3.87)	19 (3.04)	24 (4.27)	8 (6.11)		
	Place of Residence (%)						< .001	.27
		Town	156 (11.83)	92 (14.70)	49 (8.72)	15 (11.45)		
		Outskirts of town	327 (24.79)	185 (29.55)	116 (20.64)	26 (19.85)		
		Village	644 (48.82)	270 (43.13)	303 (53.91)	71 (54.20)		
		Countryside	192 (14.56)	79 (12.62)	94 (16.73)	19 (14.50)		
	Income in CHF (%)						.25	.11
		< 2500	68 (5.16)	29 (4.63)	35 (6.23)	4 (3.05)		
		2501–5000	203 (15.39)	90 (14.38)	91 (16.19)	22 (16.79)		
		5001–7500	418 (31.69)	204 (32.59)	176 (31.32)	38 (29.01)		
		7501–10,000	220 (16.68)	107 (17.09)	87 (15.48)	26 (19.85)		
		>10,000	137 (10.39)	78 (12.46)	50 (8.90)	9 (6.87)		
		Not declared	273 (20.70)	118 (18.85)	123 (21.89)	32 (24.43)		
	Nationality (%)						.03	.13
		Swiss	1195 (90.60)	554 (88.50)	520 (92.53)	121 (92.37)		
		German	56 (4.25)	36 (5.75)	17 (3.02)	3 (2.29)		
		Other	54 (4.09)	32 (5.11)	16 (2.85)	6 (4.58)		
		Not declared	14 (1.06)	4 (0.64)	9 (1.60)	1 (0.76)		
**Physical activity measures**								
	Self-reported moderate to vigorous physical activity^e^ (hours/week)						< .001	.03
		Mean (SD)	8.90 (11.10)	8.96 (11.38)	8.75 (10.59)	9.26 (11.25)		
		Median	6.00	6.00	6.00	5.25		
	Self-reported walking^e^ (hours/week)						<.001	.03
		Mean (SD)	10.01 (13.70)	10.31 (13.44)	9.99 (15.55)	8.61 (10.87)		
		Median	6.00	6.54	6.00	4.50		
	Physical activity at work		3.45 (1.88)	3.37 (1.84)	3.48 (1.91)	3.67 (1.90)	< .001	.009
	Physical activity during spare time		5.26 (1.17)	5.36 (1.19)	5.19 (1.13)	5.09 (1.22)	.06	.003
	Walking on way to work (%)							
		Yes	234 (17.74)	126 (20.13)	87 (15.48)	21 (16.03)	.10	.06
		No	1085 (82.26)	500 (79.87)	475 (84.52)	110 (84.97)		
**Other**								
	Subjective health status		3.60 (0.73)	3.66 (0.73)	3.55 (0.71)	3.53 (0.80)	<.001	.02
	Pedometer brand (%)						.73	.09
		Fitbit	832 (62.08)	387 (61.82)	359 (63.88)	86 (65.65)		
		Fitbit App	284 (21.53)	141 (22.52)	121 (21.53)	22 (16.79)		
		Garmin	138 (10.46)	69 (11.02)	55 (9.79)	14 (10.69)		
		Jawbone	65 (4.93)	29 (4.63)	27 (4.80)	9 (6.87)		
	Pedometer bought for participation (%)						.04	.07
		Yes	709 (53.75)	316 (50.48)	325 (57.83)	68 (51.91)		
		No	571 (43.29)	289 (46.17)	221 (39.32)	61 (46.56)		
		Not declared	39 (2.96)	21 (3.35)	16 (2.85)	2 (1.53)		
	Participation of family member or friend						.65	.03
		Yes	251 (19.03)	122 (19.49)	108 (19.22)	21 (16.03)		
		No	1068 (80.97)	504 (80.51)	454 (80.78)	110 (83.97)		

^a^ Unless otherwise indicated, mean (SD) are displayed for continuous variables and absolute frequencies (relative frequencies) are displayed for categorical variables.

^b^ η^2^ is used as a measurement of effect size for one-way ANOVAs and Cramer’s *V* is used as a measurement of effect size for chi-square test. Effect size conventions for η^2^ are: .01 (small effect), .09 (medium effect), .25 (large effect). Effect size conventions for Cramver’s *V* are: .10 (small effect), .30 (medium effect), .50 (large effect) for *df*=1 and .07 (small effect), .21 (medium effect), .35 (large effect) for *df*=2 [77].

^c^ Based on information of the Swiss Federal Office for Statistics for the year 2013 [78].

^d^Categories with expected frequencies <5 were not considered for between-group comparison.

^e^ Due to violation of normality a logarithmic transformation was applied for between-group comparison and the median is reported in addition to the mean.

## Discussion

### Strengths and Limitations

This study protocol describes the design and baseline characteristics of a longitudinal cluster-randomized controlled trial testing the effects of monetary and charitable incentives on the acceptance of and adherence to a pedometer-based health prevention program. To the best of our knowledge, this is the first study to systematically test the effects of different incentive strategies within a pedometer-based health intervention offered by a large health insurance company in western cultures. External validity has to be pointed out as a key strength of the described trial. Both study design and incentive strategies are tested in a real-world setting, thus ensuring the applicability of the results and conclusions.

When interpreting the results of this study, some limitations have to be considered: selection effects might affect the participation in the PHI. For example, by especially attracting highly motivated or physically active participants, those effects could potentially undermine the power of our analyses. However, we will be able to control our analyses for prior level of physical activity. Further, comparisons of T_2_ measures between the groups have to be interpreted with caution, because T_2_ reflects different time points for experimental and control groups. T_2_ was set at 6 months after start of the intervention for the EGs and at 3 months for the CG. However, the main focus of this study is on the acceptance of the promotion program, which is operationalized using the participation rate, and is thus not dependent on any T_2_ measurement. Lastly, the goal of reaching 10,000 steps per day on average might have detrimental motivational effects for some participants. It might be perceived as too challenging for very inactive participants or when participants were not able to achieve sufficiently high step counts for several days in a month.

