Second, rooting in the view of privacy as a commodity [48], most approaches explaining privacy disclosure behavior involve the concept of a privacy calculus (ie, weighting the costs and benefits of sharing personal information [23,24,49]). Specifically, sharing personal health data can be perceived as unfair, if no compensating benefit is provided [49]. Consequently, researchers have tried to augment the benefits of information disclosure by providing financial incentives among others in exchange for personal information [20,48,50-52]. For example, participants in a quasiexperimental setup were more willing to disclose personal information on a website for stock trading when they were offered financial gains [50]. Additionally, two-thirds of participants of a large public survey (N=1100) stated that they expect financial compensation in exchange for providing personal health-related data [53]. Thus, financial incentives can be used to increase the perceived benefits of sharing health-related information.

In conclusion, we assume the benefits of financial incentives to be 2-fold within a physical activity intervention offered by a health insurance company: first, a financial incentive may act as a benefit in the privacy calculus of potential intervention participants, compensating for possible privacy concerns. This effect should be reflected in higher participation rates for experimental groups (EG) in which a financial incentive is provided. Second, in line with previous research, financial incentives may have motivational effects and affect the treatment adherence of participants. Therefore, this study protocol describes the design and methodology in order to examine the effects of the two different incentives on the acceptance of and adherence to a pedometer-based health intervention (PHI). Demographics and baseline characteristics of study participants are presented in the results section. Subsequently, strengths and limitations of the study design are discussed.

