To avoid spill-over effects between the different incentive strategies [45], potential participants were assigned to the different groups based on their canton of residence and invitations were send out after the assignment was complete. As at the beginning of the program, the control group (CG) appeared to be the least attractive condition we wanted to contact a different number of potential participants for the 3 groups according to a proportion of 2 (EG1):2 (EG2):1 (CG/EG1). In order to do so and to further account for differences in activity preferences between urban and rural areas in Switzerland [59], cantons were grouped in blocks of 5 according to number of customers and population density. Each block contained 2 pairs of cantons that were matched for geographical proximity. The matched pairs were then randomly assigned to one of the EGs and the remaining canton was assigned to the control group. To facilitate clustering, cantons with very few customers were combined and treated as one unit. We used the approach of Gao and colleagues [60] for nonaggregate cluster-randomized controlled trials with binary outcomes to estimate the number of participants to be contacted in order to detect an expected difference in participation rate. Being conservative in comparison to public polls [53] and studies [11], we expected a difference of 5% in participation rates (8% participation was expected for both intervention groups vs 3% for the control group). As participants in our study were clustered, a potential design effect had to be considered [60]. An assumed intracluster-correlation of .01 (according to [61]) and the average cluster size of mean (M) = 925 (standard deviation [SD] = 1356) yielded a design effect of 10.24. Thus, in order for the difference in participation rates to be significant at least 15,725 customers needed to be contacted (6475 for each experimental group and 2775 for the control group). We met this requirement by directly contacting 18,638 customers via email before the beginning of the PHI.

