The following variables were measured for analysis: the participation rate represents the primary outcome and is measured by calculating the participation rate in total and for the different groups, respectively. Participation rate is defined as the proportion of active participants that is participants that shared their data with the Web-based platform of the insurance company at least once. Secondary outcomes are continued use of the pedometer, performance of the participants, and health condition. The number of days at which participants share their step count with their health insurance company is used as an indicator of the continued use of the pedometer. The number of steps and the amount of money saved or donated indicate the performance of the participants. Apart from the number of steps, physical activity was also assessed by questionnaire measures namely hours of moderate to vigorous physical activity and hours of walking per week at T_1_ and T_2_ (based on the International Physical Activity Questionnaire [65,66]), walking on the way to work, physical activity at work, and during spare time at T_1_ and T_2_. The proportion of money saved versus donated (at T_1_ and T_2_) is further used to evaluate the charitable incentive condition. We use health perception at T_1_ and T_2_ (“How would you rate your overall health status?”) [67-69] and improvement of health perception due to the intervention at T_2_ (eg, “In general, my health improved due to the prevention program”) [67-69] as subjective measures and service billing with the health insurance company (ie, amount of money repaid by the insurance company per participant) after completion of the prevention program and 1 year later as objective measures in order to assess effects on participants’ health condition. Unless otherwise indicated, a 7-point Likert scale, from strongly disagree (1) to strongly agree (7), will be used for items requiring a response scale.

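### Secondary incentive-versus-control comparisons are made among people who joined after randomisation; the article treats selection as a loss of power, but it is also a source of bias of unknown direction

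*Protocol article*

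**What the plan says.** The Introduction expects the incentive to alter joining: "This effect should be reflected in higher participation rates for experimental groups (EG) in which a financial incentive is provided". Participant Acquisition and Sample puts figures on this: "8% participation was expected for both intervention groups vs 3% for the control group". The same section says that assignment by canton was complete before invitations were sent, so joining is a post-randomisation event.

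Data Collection and Variables defines the secondary outcomes on those who joined. For continued use: "The number of days at which participants share their step count with their health insurance company is used as an indicator". Performance is the participants' steps and money earned or donated, perceived health comes from participants' questionnaires, and billing is an amount per participant. Data Analysis nests step counts within participants.

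On selection, Strengths and Limitations says that "by especially attracting highly motivated or physically active participants, those effects could potentially undermine the power of our analyses", and answers that prior activity can be controlled for. Baseline Characteristics adds place of residence and subjective health as covariates and lets the groups have different intercepts for baseline activity. Data Collection and Variables also lists control variables to be measured against confounding.

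**The concern.** Randomisation makes the contacted customers comparable across groups, apart from chance differences between cantons. It does not make the joiners comparable when the treatment itself changes who joins. A difference in days shared or in steps between incentive and control joiners can then reflect an effect of the incentive on behaviour, a different mix of people, or both.

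The article names the mechanism, selection of motivated or active people, but gives its consequence only as reduced power. A loss of power makes a true effect harder to find. Differential selection can also create an effect that is not there, or hide or reverse a real one. Adherence is part of the stated objective, so this affects what the trial may conclude on it.

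**Working it through.** **1. The plan's own figures.** From "An assumed intracluster-correlation of .01 (according to [61]) and the average cluster size of mean (M) = 925", the design effect is 1 + (925 − 1) × 0.01 = 10.24, as stated. The power is not given. Assume 80%, two-sided 5%, and the 7:3 ratio implied by 6475:2775. Then 3% against 8% needs 247 controls before inflation.
- Control: 247 × 10.24 = 2529, or 2.73 clusters of 925. Rounded up to 3, this is 2775.
- Each incentive arm: 247 × 7/3 × 10.24 = 5902, or 6.38 clusters. Rounded up to 7, this is 6475.
- Total: 2775 + 6475 + 6475 = 15,725, as stated.

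So 8% and 3% are the working rates behind the sample size, and the plan is built on a large difference in joining.

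**2. Joining so far.** T1 survey participants (Survey Participation) over customers contacted (Table 1):
- Financial: 626/7487 = 8.36%
- Charitable: 562/8216 = 6.84%
- Control: 131/2935 = 4.46%

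This is a proxy. The participation rate is defined by having shared data at least once, and survey counts may differ from it.

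**3. Share of incentive-arm joiners who would not have joined under control.** If the incentive deters nobody, the share is s = 1 − p(control)/p(incentive).
- Planned: 1 − 3/8 = 62.5%
- Financial, proxy: 1 − 4.46/8.36 = about 47%
- Charitable, proxy: 1 − 4.46/6.84 = about 35%

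If the incentive deters some people who would otherwise join, each share is larger, so these are minimum values at the given rates.

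**4. What this does to a joiner-only contrast.** Suppose the incentive has no effect on the outcome and deters nobody. Then the expected difference between incentive and control joiners is s × δ, where δ is the mean outcome of the added joiners minus that of people who would join anyway. It is zero only if δ is zero, and its sign is the sign of δ, which the document does not give.

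**5. Illustrative size (assumption).** Let joiners be the top fraction p of a normal propensity to join that correlates ρ with the outcome, with no incentive effect. The spurious difference in SD units is ρ × [m(p incentive) − m(p control)], where m(p) is the normal density at the cut-off divided by p. At the planned rates m(0.08) = 1.858 and m(0.03) = 2.268, a difference of −0.410. For ρ from 0.1 to 0.5:
- Planned rates: −0.04 to −0.21 SD; a nominal 5% test rejects in about 6% to 50% of trials (518 and 83 joiners)
- Financial, proxy: −0.03 to −0.14 SD; about 6% to 36%
- Charitable, proxy: −0.02 to −0.09 SD; about 5% to 18%

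The rejection rates treat joiners as independent. A negative ρ reverses the sign.

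**6. Does Table 1 show the direction?** No. Financial joiners report more spare-time activity than control joiners (5.36 against 5.09, standardised difference 0.23) and better subjective health (3.66 against 3.53, 0.18), but less activity at work (3.37 against 3.67). For charitable against control, the spare-time and health differences are 0.09 and 0.03. With 8, 11 and 7 cantons per group, canton imbalance could produce such differences as well as selection could.

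**7. Do the planned adjustments remove it?** The stated covariates are residence and subjective health, with control for prior activity. They come from a questionnaire answered after joining. Motivation, which the limitation itself names, is not among them. No step count before the programme is described, so a group-specific intercept in the step model combines selection with any immediate incentive effect.

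**The case against.** The plan does not ignore group differences. It measures a long list of control variables, commits to covariates and group intercepts, and says that acceptance, the primary outcome, is its main focus. That outcome uses everyone contacted and is untouched. The financial and charitable groups are planned at the same 8%, so the uptake gap does not arise between them at planning rates, although the mix of joiners could still differ. A condensed article may also leave sensitivity analyses to a fuller plan. All of this stands, but none of it corrects a limitation that gives power as the only consequence of selection.

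An analysis over all contacted customers does not isolate adherence either. Even with no effect on joiners' behaviour, it would favour the incentive through uptake alone, which the primary outcome already measures. The Introduction's interest is in adherence among participants. This also stands, and is why that analysis belongs beside the joiner-only models and not in their place.

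A reader might infer more than the document supports:
- That the incentive groups will look worse because incentives attract less motivated people. Table 1 does not support that direction, and the opposite is equally possible.
- That the adherence question goes unanswered. The joiner-only contrast is informative but not protected by randomisation.
- That billing can be analysed for everyone contacted. The article describes billing data for participants, under privacy terms accepted on joining, and does not show access for others.

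**Conclusion.** The point holds for the incentive-versus-control comparisons of continued use, steps, perceived health and billing. They condition on joining, which the incentive is designed to change, and the article names only a loss of power. The share of incentive-arm joiners without a counterpart in control is 62.5% at the planned rates, or about 47% and 35% by the survey proxy, if the incentive deters nobody. The resulting bias has unknown sign. Its size depends on how far added joiners differ from those who would join anyway, which the document does not give; the SD figures above are illustrations under an assumed correlation. The planned adjustments may reduce the bias but cannot be relied on to remove it. This should be corrected before the adherence results are interpreted. It does not threaten the primary result.

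**What to change.** 1. In Strengths and Limitations, say that selection can bias the incentive-versus-control comparisons of secondary outcomes as well as reduce power, and label the joiner-only comparisons as non-randomised.
2. Beside them, add an analysis over all contacted customers, by canton unit, of days shared in months 1-3 and of the number of those months in which the programme recorded an average reaching 7500 or 10,000 steps, with non-joiners scored 0. The window ends at month 3 because control participants can earn rewards from month 4.
3. Show participation and adherence among joiners separately next to the combined figure. Report how many participants had their data deleted, which the Procedure section allows, and do not silently score them 0.
4. Extend this to billing only if the insurer can supply totals for all contacted customers.

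The cost is a modest extra analysis, using counts of contacted customers already reported and step records already held on the platform. The downside is that the per-customer figure mixes uptake with adherence and measures attainment recorded by the programme, not how much non-joiners walk. It therefore does not isolate a motivational effect.
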